#### Eligibility of Patients

Treatment initiation with siponimod as routine therapy is at the discretion of the treating physician. The decision for siponimod treatment according to drug label information needs to be made before enrollment and independently of study participation. Participants of all genders are eligible if they are 18 years or older, are diagnosed with SPMS, and provide written informed consent. Patients will be excluded due to off-label therapy, pregnancy and breastfeeding, treatment with siponimod before enrollment, and participation in interventional trials or PANGAEA 2.0 EVOLUTION. Patients who do not attend study visits for more than 12 months will exit the study.

### Procedures

#### Dose Titration

After treatment decision and for dose selection, genetic variants of CYP2C9, a cytochrome P450 isoform involved in the metabolism of exogenous compounds by the liver [48], need to be determined in SPMS patients before the first dose of siponimod [34]. These CYP2C9 variants exhibit reduced enzymatic activity, leading to substantially elevated siponimod plasma levels [49,50]. Patients with CYP2C9 genotypes *1*1, *1*2, and *2*2 as well as patients with CYP2C9 genotypes *1*3 or *2*3 undergo a 5-day titration phase. In this titration phase, dosage is gradually increased from days 1 and 2 (0.25 mg) to day 3 (0.5 mg), day 4 (0.75 mg), and day 5 (1.25 mg). The maintenance dose is then 2 mg (CYP2C9*1*1, *1*2, *2*2) or 1 mg (CYP2C9*1*3, *2*3) taken orally once daily. If one dose is missed during the first 6 days of treatment or treatment at maintenance dose is interrupted for 4 or more consecutive days, titration needs to be reinitiated. Siponimod is contraindicated in patients with CYP2C9*3*3 genotype.

In patients with pre-existing cardiac conditions (ie, sinus bradycardia, first-degree or second-degree AV block, or a history of myocardial infarction or heart failure), a first-dose 6-hour monitoring of pulse and blood pressure is recommended, with an electrocardiogram at the beginning and end. Additional monitoring in case of clinically relevant cardiac symptoms as well as appropriate clinical management will be initiated according to the product information [34]. In AMASIA, SPMS diagnosis according to ICD-10, demographic and clinical data including MS-disease and non-MS-disease history, and varicella zoster virus immune status will be obtained during the initial dose titration phase. Varicella zoster virus vaccination of antibody-negative patients is recommended prior to siponimod treatment.

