#### Propensity Score–Matched Comparison With PANGAEA 2.0 EVOLUTION

The real-world evidence study PANGAEA 2.0 [8] has been expanded by the EVOLUTION study arms [9] to clinically characterize SPMS patients and RRMS patients at risk for SPMS. In EVOLUTION, patients aged 18 to 65 years and with moderate to severe disability (EDSS 3.0-6.5) are included if they were previously diagnosed with RRMS and have a current diagnosis of SPMS or RRMS at risk for SPMS. Treatment options at inclusion are current disease-modifying therapies or no treatment during the last 12 months. Any treatment option as well as change of treatment are permitted, thereby representing the standard of care for SPMS prior to availability of siponimod. By having aligned the objectives and measures of EVOLUTION and AMASIA, it will be feasible to compare the demographic and clinical parameters as well as the disease impact on functional domains, cognition, quality of life, and socioeconomic parameters. Since patients in EVOLUTION receive standard of care currently available to these patients, the propensity score–matched comparison with data obtained by AMASIA will provide further insights into the long-term effectiveness and safety of siponimod in clinical practice (Figure 4).

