### Statistical Analysis

For analysis, descriptive statistics will be primarily used. The full analysis set includes all patients receiving at least one dose of siponimod with at least one available post-dose data recording. Sample statistics such as median, mean (SD), minimum, maximum, 5% percentile, 1st quartile, 3rd quartile, 95% percentile, and number of valid and missing values will be presented in tabular form. Distributions of absolute and relative frequencies will be reported for nominal and ordinal-level data. Incidence rates of all safety outcomes (events per patient-year) will be evaluated for the patient population included. A propensity score matching adjustment, possibly using a caliper-based nearest-neighbor approach as seen in Alsop et al [66], will be used to compare data from AMASIA with data from the PANGAE 2.0 EVOLUTION arm. Possible predictive baseline and prestudy variables to be included in the model are as follows: age at baseline (years), sex, time since diagnosis at baseline (years), treatment at baseline, number of relapses in the past 12 months before baseline, and EDSS score at baseline. A multivariable logistic regression model will be fitted with the treatment arm as the dependent variable. The distribution of propensity scores before and after matching will be analyzed. Using the Medical Dictionary for Regulatory Activities, AEs are categorized according to system organ class and preferred term for individual adverse events (for AEs, serious AEs, adverse drug reactions, serious adverse drug reactions). For all analyses, SAS version 9.2 will be used.

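### The candidate propensity variables contain no measure of general health, so the matched AMASIA–EVOLUTION comparison, mainly on safety, is open to residual confounding by comorbidity in a direction the documents do not settle

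*Protocol article*

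**What the plan says.** **Entry to AMASIA.** Under Eligibility of Patients, "Treatment initiation with siponimod as routine therapy is at the discretion of the treating physician", and "The decision for siponimod treatment according to drug label information needs to be made before enrollment and independently of study participation". The same section states: "Patients will be excluded due to off-label therapy, pregnancy and breastfeeding, treatment with siponimod before enrollment". Study Design likewise leaves diagnosis and the treatment decision to the physician, following the label, before enrolment.

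**Entry to EVOLUTION.** The section on the propensity score–matched comparison gives an age range of 18 to 65 years, an EDSS range of 3.0 to 6.5, and a diagnosis requirement. Any therapy, a change of therapy, or no treatment in the preceding 12 months is allowed. No criterion of suitability for siponimod is described.

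**The propensity model.** Statistical Analysis offers these as possible variables: "age at baseline (years), sex, time since diagnosis at baseline (years), treatment at baseline, number of relapses in the past 12 months before baseline", and finally baseline EDSS. Study membership is the dependent variable in a logistic regression, and caliper-based nearest-neighbour matching is mentioned as a possibility.

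**What AMASIA records.** Dose Titration lists "demographic and clinical data including MS-disease and non-MS-disease history" among the data obtained at the start.

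**What the comparison is for.** It "will provide further insights into the long-term effectiveness and safety of siponimod in clinical practice". The Discussion adds that it will extend the safety and efficacy profile, and says that sample size, population characteristics, observation length, visit interval and choice of tests guarantee comparability. The closing summary repeats the expectation for effectiveness and safety.

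**The concern.** One cohort consists of people judged suitable for a particular drug. The other, as described, does not. Physicians weigh general health in such a judgement, so the cohorts may differ in comorbidity even among patients alike in age, sex, disease duration, treatment, relapses and EDSS.

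Comorbidity plausibly drives serious adverse events, which the article defines to include hospitalisations, and it may also affect walking, quality of life and resource use. If it differs between the matched sets, part of any safety difference would reflect who was given siponimod rather than what siponimod did. The safety contrast is the most exposed, because all six candidates describe demography or MS and none describes other illness.

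**Working it through.** **The plan's own figures.** Sample Size gives 1000 completers, a precision of 3.0% and 13% annual dropout from 1500 recruited. With 62.2% free of progression and an assumed 95% interval, the half-width is 1.96 × √(0.622 × 0.378 / 1000) = 3.0%. Completers: 1500 × 0.87³ = 988. These reproduce closely, but they concern a single-arm estimate and are unaffected by this point. The article gives no figure for the matched comparison.

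**Do the listed variables reach comorbidity?** Only indirectly. Matching on age, sex, time since diagnosis and EDSS balances whatever part of comorbidity moves with them. What matters is the imbalance left after matching, so the prevalences below are to be read as post-matching values.

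**Illustration for safety.** The documents give neither comorbidity prevalences nor event rates, so every input is an assumption. Take a serious-event rate of 0.20 per patient-year with a relevant comorbidity and 0.08 without, and no drug effect. With prevalence a in AMASIA and e in EVOLUTION:

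rate ratio = [0.20a + 0.08(1 − a)] / [0.20e + 0.08(1 − e)]

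| a | e | Calculation | Ratio with no drug effect |
|---|---|---|---|
| 10% | 15% | 0.092 / 0.098 | 0.94 |
| 5% | 15% | 0.086 / 0.098 | 0.88 |
| 5% | 25% | 0.086 / 0.110 | 0.78 |
| 15% | 15% | 0.098 / 0.098 | 1.00 |
| 15% | 5% | 0.098 / 0.086 | 1.14 |

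**Sensitivity to the strength of comorbidity.** Let RR be the assumed risk ratio for the outcome with versus without comorbidity. The spurious ratio is [1 + a(RR − 1)] / [1 + e(RR − 1)]. With e from 20% to 40%, and a from 5% to 20% but always below e, it is 0.94 to 0.99 for RR 1.2, 0.85 to 0.98 for RR 1.5, 0.75 to 0.96 for RR 2, and 0.61 to 0.93 for RR 3. Swapping the two prevalences gives the reciprocals.

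**Illustration for progression.** Use EXPAND's placebo proportion as a stand-in for EVOLUTION: 100 − 52.3 = 47.7% progressing. The rate without comorbidity is then 47.7% / [1 + e(RR − 1)], and the AMASIA rate with no drug effect is that value times [1 + a(RR − 1)].

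- Low case, e = 30%, a = 20%, RR 1.2: 47.7 / 1.06 = 45.0; 45.0 × 1.04 = 46.8; difference 0.9 points.
- High case, e = 30%, a = 10%, RR 1.5: 47.7 / 1.15 = 41.48; 41.48 × 1.05 = 43.55; difference 4.15 points.

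The siponimod–placebo difference quoted from EXPAND is 62.2 − 52.3 = 9.9 points. At RR 1.0 the spurious difference is zero.

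**The case against.** **The list is provisional.** The variables are introduced as possible ones, and the final model may stand in a document not shown. This weighs against calling the plan wrong. It does not remove the point: the article chose to name candidates, all of one kind, and rests claims about comparability on the matched comparison.

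**The cardiac text is not a filter.** A reader might infer that AMASIA patients are chosen by a cardiac work-up that EVOLUTION patients never pass. The text does not support that. "In patients with pre-existing cardiac conditions (ie, sinus bradycardia, first-degree or second-degree AV block, or a history of myocardial infarction or heart failure" opens a recommendation to monitor the first dose in patients who are being started, so such patients do enter. No EVOLUTION work-up is described either way. The only selection the text shows is physician judgement under the label.

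**The direction is open.** AMASIA states no upper age limit, and the Discussion describes it, after a reference to EXPAND, as unrestricted for comorbidity and baseline EDSS. EVOLUTION is bounded on age and EDSS. More comorbidity in AMASIA is therefore possible, although matching on age and EDSS would remove part of it. The absence of an entry rule also does not show that the matched sets are balanced.

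**The limits are acknowledged.** The Discussion names lack of randomisation and patient heterogeneity, but only for conclusions on efficacy, and then offers the matched comparison as the response.

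**The remedy may be out of reach.** Nothing shows that EVOLUTION records comorbidity. This stands, and a fallback is needed. Screening comparators against siponimod's contraindications is not a workable alternative from these documents. Apart from "Siponimod is contraindicated in patients with CYP2C9*3*3 genotype" and the exclusion of pregnancy and breastfeeding, they do not list what the label rules out, and nothing shows that EVOLUTION genotyped its patients.

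**Conclusion.** The point holds as a low-cost improvement to a stated covariate list. The candidates omit general health, selection by physician judgement under the siponimod label applies to one cohort only as described, and AMASIA already holds relevant baseline data. The matched comparison is therefore open to residual confounding by comorbidity, and the assurance of comparability goes further than the design allows.

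The size rests wholly on assumed inputs: no-effect rate ratios of 0.78 to 1.14 in the worked safety scenarios, and 0.90 to 4.15 points on progression when EVOLUTION is assumed to carry the excess. Equal prevalence after matching gives no bias. A reader might conclude that the contrast is confounded, or that matching cannot balance comorbidity at all. Neither follows, because the final model is not shown, the prevalences are unknown and the listed variables capture part of it. Safety is the main exposure. The effect on progression depends on how strongly comorbidity predicts it, which the documents do not give. The single-arm primary estimate is not affected.

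**What to change.** In Statistical Analysis, add comorbidity derived from the non-MS-disease history to the candidate propensity variables, for example cardiac history and a comorbidity count, defined identically in both cohorts. Report its balance before and after matching alongside the propensity score distributions.

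Establish first whether EVOLUTION holds the field. If it does not, either confine the safety statements in the matched-comparison section, the Discussion and its closing summary to a description of AMASIA's own patients, or accompany the comparison with a sensitivity analysis for unmeasured confounding. In either case, soften the Discussion's assurance of comparability so that it refers to the characteristics actually matched.

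The cost is plan wording and use of data AMASIA already collects. The downside is a somewhat smaller matched set and dependence on EVOLUTION's records.

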#### Observational Phase

Assessments during the 3-year observational period are depicted in Figure 3. Data on clinical examinations and MS disease status are obtained quarterly, if available. Data on MS disease status include MRI findings concerning number and volume of T2 hyperintense lesions, Gd-enhancing lesions, T1 hypointense lesions, and brain volume changes as well as EDSS and MS activity scale scores. The latter documents time, duration, intensity, treatment, and recovery of relapses.

Results of functional tests and questionnaires are obtained every 6 months (except for the questionnaire on the quality of life of caregivers [51]). Functional tests comprise the SDMT [36], timed 25-foot walk [52,53], and the nine-hole peg test [54] to assess neurological dysfunction and disability of lower and upper extremities. Furthermore, different questionnaires address the patients’ [55-58], physicians’ [59,60], and relatives’ perspectives as well as socioeconomic aspects [61]. Disease progression will be additionally judged by means of a progression questionnaire aligned with the online tool MSProDiscuss, which is intended to facilitate the discussion between physicians and patients about SPMS [42,60].

Occurrence, duration, causal relationship to therapy, counteractive measures to and outcomes of AEs, and treatment discontinuation and interruption will be documented throughout the study. AEs are defined as any unfavorable change in the patients’ pretreatment condition, regardless of their potential relation to treatment and irrespective of whether medication was taken as intended. Serious AEs comprise lethal or life-threatening events leading to persistent or significant disability, congenital anomaly or birth, hospitalizations, and other medically significant events that compromise the safety of patients.

**Figure 3 figure3:**
[figure not shown]
Study visits during AMASIA (imp**A**ct of **M**ayzent [siponimod] on second**A**ry progressive multiple **S**clerosis patients in a long-term non-**I**nterventional study in Germ**A**ny). 9Hole Peg test: nine-hole peg test; AE: adverse event; CBC: complete blood count; CGI: clinical global impression; EDSS: Expanded Disability Status Scale; FSMC: Fatigue Scale For Motor And Cognitive Functions; MRI: magnetic resonance imaging; MS: multiple sclerosis; MS-AS: MS activity scale; MS-HRS: Multiple Sclerosis Health Resource Utilization Survey; SAE: serious adverse event; SDMT: symbol digit modalities test; T25-FW: timed 25-foot walk; TSQM-9: Treatment Satisfaction Questionnaire for Medication; UKNDS: United Kingdom Neurological Disability Scale.

#### Propensity Score–Matched Comparison With PANGAEA 2.0 EVOLUTION

The real-world evidence study PANGAEA 2.0 [8] has been expanded by the EVOLUTION study arms [9] to clinically characterize SPMS patients and RRMS patients at risk for SPMS. In EVOLUTION, patients aged 18 to 65 years and with moderate to severe disability (EDSS 3.0-6.5) are included if they were previously diagnosed with RRMS and have a current diagnosis of SPMS or RRMS at risk for SPMS. Treatment options at inclusion are current disease-modifying therapies or no treatment during the last 12 months. Any treatment option as well as change of treatment are permitted, thereby representing the standard of care for SPMS prior to availability of siponimod. By having aligned the objectives and measures of EVOLUTION and AMASIA, it will be feasible to compare the demographic and clinical parameters as well as the disease impact on functional domains, cognition, quality of life, and socioeconomic parameters. Since patients in EVOLUTION receive standard of care currently available to these patients, the propensity score–matched comparison with data obtained by AMASIA will provide further insights into the long-term effectiveness and safety of siponimod in clinical practice (Figure 4).

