**Figure 2 figure2:**
[figure not shown]
Study design of AMASIA (imp**A**ct of **M**ayzent [siponimod] on second**A**ry progressive multiple **S**clerosis patients in a long-term non-**I**nterventional study in Germ**A**ny), a non-interventional study involving an initial dose titration (visit 1), followed by a 3-year observational phase (visits 2-13).

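### The matched comparison counts AMASIA patients from a siponimod start and EVOLUTION patients from study inclusion, and no listed matching variable aligns the two clocks

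*Protocol article*

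**What the plan says.** **AMASIA.** Eligibility of Patients states: "Patients will be excluded due to off-label therapy, pregnancy and breastfeeding, treatment with siponimod before enrollment". The Figure 2 caption makes visit 1 the dose titration and visits 2 to 13 the three-year observation. Study Design restricts the population to active disease, shown by relapse or MRI. Follow-up therefore begins at drug start.

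**EVOLUTION.** The section on the matched comparison describes entry thus: "Treatment options at inclusion are current disease-modifying therapies or no treatment during the last 12 months". It adds: "Any treatment option as well as change of treatment are permitted, thereby representing the standard of care for SPMS prior to availability of siponimod". The article states no requirement that a treatment be started, and no activity criterion. Follow-up begins at study inclusion.

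**The comparison.** The same section says that "the propensity score–matched comparison with data obtained by AMASIA will provide further insights into the long-term effectiveness and safety of siponimod in clinical practice". Statistical Analysis names six candidate propensity variables: age, sex, time since diagnosis, treatment at baseline, relapses in the previous 12 months, and EDSS. For safety it says: "Incidence rates of all safety outcomes (events per patient-year) will be evaluated for the patient population included". The Discussion presents comparability as secured by study size, patient mix, duration of observation, spacing of visits and choice of tests. Its limitations paragraph names non-randomisation, patient heterogeneity and incomplete visit data, but not the different start of the clock.

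**The concern.** Equal length of observation does not put two cohorts at the same point relative to a treatment start. Every AMASIA patient contributes the weeks just after starting a drug. An EVOLUTION patient contributes such weeks only if the current therapy happens to be recent or a switch occurs later.

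For safety, a single rate per patient-year over three years mixes initiation with long-term exposure in one cohort and much less so in the other. For effectiveness, one cohort starts at a treatment decision in active disease, and the other at an inclusion visit with no stated link to either. A difference between the matched groups could then partly reflect where each clock starts, and the reader would be told that the groups are comparable.

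**Working it through.** **1. The plan's own figures.** Inputs from Sample Size: 62.2% without progression, 1000 completers, 3.0% precision, 13% annual dropout, 1500 recruited. A two-sided 95% level is assumed, as none is stated.
- Half-width = 1.96 × √(0.622 × 0.378 / 1000) = 3.005%.
- Recruitment = 1000 / 0.87³ = 1000 / 0.6585 = 1519, against 1500 stated. Conversely, 1500 × 0.6585 = 988 completers, with a half-width of 3.02%.

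These figures reproduce to rounding. They concern the single-arm estimate, which the present point does not touch. The article gives no separate sample size for the matched comparison.

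**2. Can the listed variables align the clocks?**
- Age, sex and time since diagnosis do not date a treatment start.
- Relapses in the previous 12 months and EDSS reduce an imbalance in disease activity but do not date a start. MRI activity, the other route to active disease in AMASIA, is not listed.
- Treatment at baseline comes closest. Read as study treatment, it is the exposure being compared. Read as prior treatment, it says what was taken but not since when.

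**3. Safety illustration (all inputs assumed).** Take two equally safe treatments. The event rate is k times background for the first m months after any start, and background afterwards. Over T months the relative rate in starters is A = (k·m + T − m) / T. If a share s of comparators is also at a start, the comparator's relative rate is s·A + (1 − s). The spurious rate ratio is the first divided by the second.

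| T | k, m | s = 0 | s = 0.5 |
|---|---|---|---|
| 36 | 1.5, 3 | (4.5 + 33)/36 = 1.04 | 1.042/1.021 = 1.02 |
| 36 | 3, 6 | (18 + 30)/36 = 1.33 | 1.333/1.167 = 1.14 |
| 12 | 1.5, 3 | (4.5 + 9)/12 = 1.13 | 1.125/1.0625 = 1.06 |
| 12 | 3, 6 | (18 + 6)/12 = 2.00 | 2.00/1.50 = 1.33 |

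**4. Effectiveness illustration (clock effect assumed).** Progression under siponimod is 100 − 62.2 = 37.8%. Suppose there is no true effect, but the different clock multiplies the comparator's risk by 0.8 to 1.25. The comparator then progresses in 30.2% to 47.3%, a spurious difference of −7.6 to +9.5 points. The siponimod–placebo difference quoted from EXPAND is 62.2 − 52.3 = 9.9 points. A clock effect of this assumed size would be of the same order as the treatment effect that the article cites.

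**The case against.** **The mismatch is not total.** A current therapy may have been started recently, and any change of treatment is permitted, so starts also occur in EVOLUTION. This stands; the right-hand column of the table shows how far it shrinks the effect.

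**No between-study safety rate ratio is specified.** The rates per patient-year are described for the included population, and neither the list of parameters to be compared nor the Figure 4 caption names adverse events. This also stands. Yet the section says that the comparison "will provide further insights into the long-term effectiveness and safety of siponimod in clinical practice", and the Discussion repeats the safety claim, so a safety contrast is at least announced.

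**Early events are a real consequence of starting.** For the question of starting siponimod against staying on standard of care, initiation events belong in the count. That is correct, and it is why the overall rate should stay beside any windowed rate. Later windows also contain only patients who remained under observation.

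**Details belong in the analysis plan.** The matching model is worded tentatively, and a plan not shown may define an index date. But the entry rules of both studies are fixed in this article, and so is the assurance of comparability.

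**A reader might infer more.** One tempting inference is that AMASIA starts at a peak of activity, so that effectiveness is biased towards siponimod. The documents do not support that. Siponimod was newly available, so a start may reflect availability, and a delayed drug effect would act the other way. Another is a large safety distortion. If 10% of starters have an initiation event in month 1 and the background is 0.02 per year, the ratio is [(0.10 + 0.02 × 35/12)/3] / 0.02 = 2.64. The same formula gives 1.14 at 0.2 per year and 1.04 at 0.5. Because the article counts any unfavourable change as an adverse event, a low background cannot be presumed.

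**Conclusion.** The point holds as a design weakness of the matched comparison. Both entry rules are in the text, none of the candidate variables dates a start, and the Discussion asserts comparability without addressing this. The comparison is liable to bias; the documents do not show that it is biased by any given amount. For safety, early events after a start would tend to count against siponimod; under the assumptions above the ratio is 1.02 to 1.33 over 36 months. For effectiveness the sign is open.

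It would go too far to say that the study fails its objective. The stated objective is effectiveness and safety of siponimod in clinical routine, and the comparison with standard of care is an additional aim.

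**What to change.** 1. Report AMASIA adverse event rates by time since siponimod start (for example 0–3, 3–12 and 12–36 months) next to the overall rate. Show any safety contrast with EVOLUTION both overall and for the later windows, with a note on who remains in those windows. If adverse events are not to be compared, withdraw the safety claim for the matched comparison. Cost: table programming on AMASIA data.
2. Where EVOLUTION records start or switch dates, add an analysis that indexes its patients at a start or switch, and add time on current therapy or recent switch to the propensity model. Keep the inclusion-date analysis alongside. Cost: fewer comparators and shorter follow-up. The article does not show that these dates exist, so check this first.
3. In the Discussion, replace the assurance of comparability with a statement that new siponimod starters are compared with mostly ongoing users or untreated patients, and list the different time zero among the limitations. Cost: wording only.
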